**1. Project summary**

The objective of current study is to evaluate the effects of phantom exercises on phantom limb pain, mobility status, and quality of life in lower limb amputees treated with mirror therapy and routine physiotherapy. Twenty-four individuals with lower leg amputation participated in this trial and were randomly assigned to two equal groups. Limb Deficiency and Phantom Limb Questionnaire was used for screening of the participants. Other tools were Visual analogue scale (pain), Amputee mobility predictor (Ambulatory status) and 36-Item Short-Form Health Survey questionnaire (Health-related quality of life). The study was conducted in 12 months and data obtained was analysed through Statistical Package for Social Sciences (SPSS) 25.0 (*IBM, New York, USA*). The intervention lasted for 4 weeks. The control group underwent mirror therapy and conventional physical therapy while the experimental group performed phantom exercises additionally. Data was collected at baseline, after two and four weeks of intervention using. Mean age of the participants in experimental and control groups was 45.3±11.1 years and 40.5±12.5 years respectively. Both groups were comparable at baseline. After intervention, pain was significantly lower in the experimental group (p<0.05). Similarly, the experimental group demonstrated significantly better score in the “bodily pain” domain of SF-36 (p<0.05). Both groups improved in other domains of SF-36 and ambulatory potential with no significantly between-group differences after intervention. It was concluded that addition of phantom exercises resulted in significantly better pain management in lower limb amputees treated with mirror therapy and routine physiotherapy.

**2. Rationale & background information**

Limb amputation negatively affects psychological, social and physical health of the patients (1). Phantom limb pain (PLP) is a common complaint after lower limb amputation can be defined as discomfort or pain in missing part of the limb. According to the literature, the incidence of PLP ranges from 42.2% to 78.8% of all cases, while the reported prevalence is 45-85% (2). Although PLP subsides with time in most patients irrespective of the cause of amputation, it persists for several years in 5-10% cases (3). PLP is distinguishable from residual limb pain (RLP) since RLP originates from physical impairments such as skin conditions, vascular abnormalities, impaired healing process, neuromas, soft tissue and bone disorders, etc. (4, 5).

One of the foremost causes of PLP is history of chronic pain (e.g., due to diabetes or peripheral vascular disease) in the affected limb before amputation. Other causative factors include seasonal changes, infections, defecation movements, urination, etc. (6). Multiple mechanisms are reported to be involved in PLP, such as spinal, supraspinal and peripheral although there is no consensus on the exact mechanism of PLP (7, 8). It has been suggested that multiple neurological mechanisms are responsible for PLP and RLP (9). PLP may deteriorate several important concepts of health-related quality of life (QOL) such as mood, sleep, independence, emotional health or relationship with family and friends, etc. (10)

One of the methods for subjectively evaluating the limb amputees in detail is limb Deficiency and phantom limb questionnaire (11). Similarly, several strategies and resources are available for evaluating the mental and physical health of amputees during rehabilitation. One of such tools is Amputee Mobility Predictor (AMP) which is an easy and reliable way of assessing ambulatory status of lower limb amputees, with or without the prosthesis. The severity of phantom limb pain can be subjectively assessed with Visual Analogue Scale (12). As for quality of life, one of the more commonly used instrument is 36-Item Short Form Survey (SF-36) which evaluates eight health domains: physical functioning, bodily pain, role limitations due to physical health problems, role limitations due to personal or emotional problems, emotional well-being, social functioning, energy/fatigue, and general health perceptions (13).

More than two dozen strategies can be found in the literature for the management of PLP. However, there is no broad consensus on the best and most effective option. One of the rehabilitation strategies for PLP which has shown promise in recent years is mirror therapy (MT). In MT, a mirror is placed in a way that allows amputee to view the reflection of the sound limb which is positioned near the mirror and its reflection is visualized by the patient while the residual limb is placed behind the mirror. This position creates an illusion of having both extremities intact, afterwards the patient moves intact extremity in different patterns. This tricks patient’s brain as if their painful phantom limb is painless and can move easily. Exact mechanisms of action for MT still remains uncertain. However, reintegration of sensory and motor systems, control over avoiding fear and restoration of body image might play a role. Nevertheless, it is inexpensive, safe and easy to administer therapy (14). One of the limitations of this therapy is the unclear reliability of visual feedback of amputated limb. (15)

One of the less investigated strategy for the management of PLP is phantom motor execution (PME), also known as phantom exercises. PME involves the imaginary movement of phantom limb in the brain along with performance of certain actual physical movements. Neurophysiological networking involved in PME is similar to that of actual executed physical activities of sound limb and it should be distinguished from pure imaginary activities as it follows a different neurophysiological pathway (16). Such exercises have been shown to safely and effectively relieve PLP in various types of limb amputations (17). For instance, the effectiveness of phantom exercises – versus general exercises - was evaluated in post-traumatic lower limb amputees. Significantly greater reduction in pain was observed as a result of phantom exercises (18).

As an alternative to MT, virtual reality training (VRT) can also be used to manage PLP, especially in patients with bilateral limb amputations. Despite the effectiveness of immersive virtual reality training, it uses are limited due to high cost. Because of high prevalence of PLP and its consequences on physical and mental health of amputees, there is a need to design easily administered, home-based and effective treatment protocol. The effects of phantom exercises, in conjunction with mirror therapy, for managing PLP in lower limb amputees are largely unknown. Therefore, the main objective of the current study was to evaluate the effects of phantom exercises on phantom limb pain, mobility status, and quality of life in lower limb amputees treated with mirror therapy and routine physiotherapy. It was hypothesized that addition of phantom exercises would result in significantly improved clinical outcome in all studied parameters.

**3. Study design**

The current single-blind randomized controlled trial was conducted in accordance with the guidelines outlined in the declaration of Helsinki.

**4. Methodology**

*4.1 Patient information*: The mean (standard deviation) age of patients in the experimental and control group was 45.3(11.1) years and 40.5(12.5) years correspondingly. Vast majority of the patients underwent amputation within 2 years prior to this trial (experimental group =10; control group = 11). The number of male patients in experimental and control group was 8 and 9 respectively. Most patients reported right-handedness except for 1 patient in each group. The patients were recruited via non-probability convenience sampling. Thirty lower limb amputees were screened for eligibility through Limb Deficiency and Phantom Limb Questionnaire among other criteria.

*4.2 Eligibility Criteria:*

*4.2.a Inclusion Criteria:*

- Ages Eligible for Study: 18 Years to 50 Years (Adult)
- Accepts Healthy Volunteers: No
- Unilateral lower limb amputation
- Phantom limb pain score (40-100 on VAS)
- Either gender
- Stable prosthetic situation (i.e., satisfaction with the fitting of the prosthesis) or being a non-user.

*4.2.b Exclusion Criteria:*

- Amputees with psychological/neurological impairments.
- Amputees having neuropathic pain other than phantom limb pain.
- Patients having visual-spatial impairments.
- Taking pain relief medications will also be excluded.
- Patients having residual limb pain.
- Inability to give informed consent.
- Carcinoma
- Infectious stump
- Severe hearing loss
- Any condition that restricts the movement of opposite limb, pain or limited range of motion in the intact limb
- Infectious and systematic diseases

*4.3 Sample size:* Sample size is 6 in each group calculated by openEpi (24). We included 12 patients in each group.

*4.4 Setting:* Pakistan Society for the Rehabilitation of the Disabled (PSRD) and Hope foundation for rehabilitation sciences, Lahore, Pakistan.

*4.5 Rehabilitation protocols*: Both study groups received mirror therapy (15 minutes) and routine physical therapy (20 minutes) while the experimental group was given Phantom Motor Execution (PME), also known as phantom exercises, additionally (15 minutes).

*4.5.a Phantom Motor Execution:* Phantom exercises included imagining movement of the phantom limb and attempting to execute these movements. The patients were asked:

1. About position at which they were feeling their phantom limb.
2. To place their intact limb at same position as they felt their phantom limb.
3. To move their both limbs in opposite direction.
4. To return back to their starting position. (24)

The movements included ankle inversion/eversion, flexion/extension, adduction with flexion of toes as clenching, abduction with extension of toes as unclenching. After patient feel relaxation, movements as knee flexion/ extension or hip flexion/ extension were repeated, until the PLP disappeared. (19) Phantom exercises were repeated until the PLP subsided completely with a maximum of 15 repetitions in one session.

*4.5.b Mirror therapy*: A standing flat mirror was used to perform 15 minutes of mirror therapy under physiotherapist’s supervision every day for 4 weeks. Sources of external stimulations (noise, television) were minimized, all accessories on the sound limb were removed, and patient’s comfort was ensured before the start of each session. Goals and benefits of mirror therapy were explained to the patients who were encouraged to ask questions. Pain level was measured on VAS prior to each session and rules of mirror therapy were instructed.

*4.5.c Routine physiotherapy*: The regimen comprised stretching of the tight musculature, static and dynamic muscle strengthening. Participants were also advised to keep a log of nature, frequency and duration of their physical activities. (20)

*4.6 Primary Outcome Measures:*

*4.6.a Visual analogue scale (VAS)* [ Time Frame: 4 weeks]

changes from the baseline, the visual analogue scale The VAS evaluates pain subjectively. It consists of a 100-mm line, with two endpoints representing "no pain" to "worst pain imaginable from left to right." Patients are instructed to mark on the line according to the level of pain and the same is measured

*4.6.b Amputee Mobility predictor* [ Time Frame: 4 weeks]

changes from the baseline, Amputee mobility predictor (AMP) is an amputee-specific tool for predicting ambulatory potential. This clinical test evaluates the predicted mobility of amputee with and without a prosthesis The AMP is a clinical test consisting of 20 tasks that are given a score of 0, 1, or 2 based on the amputee's performance. There is an item 21 where a score is given ranging from 0 to 5.

*4.6.c Limb Deficiency and Phantom Limb Questionnaire* [ Time Frame: day 1]

Patients will be evaluated using "Limb Deficiency and Phantom Limb Questionnaire (Questionnaire 2008, Version 2)" in order to assess their eligibility for including in this study.

This questionnaire does not have any scoring, it only concludes the questions on Yes/No basis for presence or absence of phantom limb pain.

*4.7 Secondary Outcome Measures:*

*4.7.a Short form 36 (SF-36)* [ Time Frame: 4 weeks]

changes from the baseline, the 36-Item Short-Form Health Survey questionnaire (SF-36) is a very popular instrument for evaluating Health-Related Quality of life (HRQOL). It is a widely used valid and reliable tool for measuring the (HRQOL) and it can be employed in both the healthy and diseased population such as amputees for assessing the outcome of health care services and the effect of medical intervention.

The SF-36 measures eight scales: physical functioning (PF), role physical (RP), bodily pain (BP), general health (GH), vitality (VT), social functioning (SF), role emotional (RE), and mental health (MH). Component analyses showed that there are two distinct concepts measured by the SF-36: a physical dimension, represented by the Physical Component Summary (PCS), and a mental dimension, represented by the Mental Component Summary (MCS).

*4.8 Equipment:*

Therapy mirror: A standing mirror (130 cm × 46 cm) with wooden frame and base (62 cm × 65 cm)

*4.9 Data collection*: Data was collected at baseline and at 2-week intervals until the conclusion of 4-week interventions. Visual Analogue Scale was used to quantify the intensity of pain before, during, and after the interventions. The ambulatory potential of the patients was assessed with the Amputee Mobility Predictor which consists of 21 different tasks with a maximum overall score of 39 signifying best ambulatory potential. High inter- and intra-rater reliability has been reported for AMP in the literature. Quality of life was evaluated through 36-Item Short Form Survey (SF-36) which addresses eight health domains: physical functioning, bodily pain, role limitations due to physical health problems, role limitations due to personal or emotional problems, emotional well-being, social functioning, energy/fatigue, and general health perceptions. 24 patients were randomly allocated into two groups; Interventional group and control groups. To ensure that the patients knew the differences between residual limb, phantom limb, and between phantom limb pains and postoperative wound pains rather than a questionnaire, a proper interview was conducted. Demographics and detail information about their amputation was collected using Limb Deficiency and phantom Limb Questionnaire. After which participants were guided about their treatment plan and therapist demonstrated all relevant exercises. A specially designed Boucher having illustrations and detailed information about mirror therapy and phantom exercises was also provided to all participants. For the convivence of responders in both groups all the instruction given verbally or written in brochure was in native language Urdu. All assessments were performed by the same physical therapist (AZ) at all stages of data collection for all patients.

*4.10 Data analysis*: Normality of the data was assessed through Shapiro–Wilk test. Multivariate analysis of variance was used to analyse training-induced changes in both groups. Between-group differences were computed with Mann-Whitney U test for VAS (pain) and second domain of SF-36. Independent samples t-test was used for AMP and remaining domains of SF-36. All statistical analyses were done with IBM SPSS 25.0 (*IBM, New York, USA*). Alpha level of significance was set at 0.05.

*4.11 Consort diagram:*

[figure not shown]

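### The Amputee Mobility Predictor, a primary outcome, has an item description that implies a maximum of 45 but a stated maximum of 39, and no rule in the protocol reconciles them

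*Combined protocol and SAP*

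**What the plan says.** Section 4.6 lists the AMP among the primary outcomes, as change from baseline with a 4-week time frame. Section 4.6.b gives the scoring: "The AMP is a clinical test consisting of 20 tasks that are given a score of 0, 1, or 2 based on the amputee's performance". It then adds: "There is an item 21 where a score is given ranging from 0 to 5". It prints no total.

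Section 4.9 describes the same instrument and says that it "consists of 21 different tasks with a maximum overall score of 39 signifying best ambulatory potential". It gives no item ranges.

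Two further statements bear on which form of the test was used. Section 4.6.b says: "This clinical test evaluates the predicted mobility of amputee with and without a prosthesis". The inclusion criteria in section 4.2.a admit patients with "Stable prosthetic situation (i.e., satisfaction with the fitting of the prosthesis) or being a non-user". No section says in which condition a given patient was scored, or whether the maximum depends on it.

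Sections 4.10 and 7 compare AMP between groups with an independent-samples t-test at the 0.05 level. They do not say whether the test is applied to the week-4 score or to the change, and they mention no covariate.

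**The concern.** The two sections agree on the number of items, so they appear to describe one instrument, yet the scores they allow do not end at the same point. A reader therefore cannot tell the range of a primary-outcome score, how close a group mean lies to the ceiling, or which form of the test produced it.

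This matters more here than it would for a minor endpoint. Of the three measures listed in section 4.6, the Limb Deficiency and Phantom Limb Questionnaire is said to carry no score, so AMP is one of only two scored primary outcomes. The project summary reports no significant between-group difference in ambulatory potential, against a hypothesis of improvement in every parameter studied. If some totals had been formed under one rule and others under another, the mean difference and its standard deviation would mix two scales.

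**Working it through.** **Inputs.** From section 4.6.b: 20 tasks with a highest score of 2 each, and item 21 with a highest score of 5. From section 4.9: 21 tasks and a maximum of 39. From section 4.3: 12 patients per group.

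**Item count.** 20 + 1 = 21, which agrees with section 4.9.

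**Maximum on the plain reading of section 4.6.b.** 20 × 2 + 5 = 45. The stated 39 is not reproduced. The gap is 45 − 39 = 6 points, which is 6/45 = 13.3% of a 45-point scale or 6/39 = 15.4% of a 39-point scale.

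**Simple alternative readings**

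| Reading | Sum | Gives 39? |
|---|---|---|
| 20 tasks only, item 21 left out | 20 × 2 = 40 | no |
| All 21 items scored 0 to 2 | 21 × 2 = 42 | no |
| One two-point task dropped | 19 × 2 + 5 = 43 | no |
| All 20 tasks capped at 1, plus item 21 | 20 × 1 + 5 = 25 | no |

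**What would give 39**

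- Three two-point tasks removed: 17 × 2 + 5 = 39. That leaves 18 items, which contradicts the 21 in section 4.9.
- All 21 items kept, with exactly six of the 20 tasks capped at 1: 14 × 2 + 6 × 1 + 5 = 39. This fits both item counts, but neither section states such a cap.
- A form of the test with a lower ceiling, for example one done without a prosthesis. No section gives a maximum specific to either condition.

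**Possible effect on the comparison, as an assumption only.** Suppose some patients had been totalled under a rule whose ceiling was 6 points higher, and the whole 6 points carried into their scores. Each such patient in an arm of 12 would move that arm's mean by at most 6/12 = 0.5 points. One patient totalled under different rules at two visits could show a spurious change of up to 6 points. If every patient was totalled under the same rule at every visit, the effect is zero. The documents do not say which case applies.

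**Where the maximum enters the plan.** The documents give no sample-size input, threshold, responder definition or rescaling based on the AMP maximum. The t-test uses the recorded totals and does not depend on the ceiling printed in the text.

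**The case against.** The best defence is that section 4.6.b never prints 45. It lists the scores in use (0, 1 and 2) without saying that every task can reach 2, and a version with six tasks capped at 1 would have 21 items and a maximum of 39. On that view the item description is merely incomplete. This stands as a possibility, and it is why the documents cannot be said to show that 39 is wrong. It does not remove the point, because the reader has to supply a rule that the protocol does not contain.

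The defence can add that section 4.9 has the same physical therapist doing all assessments for all patients at all stages, which makes mixed scoring less likely, and that nothing in the documents shows that totals were formed inconsistently. This also stands, and it limits the severity. It does not tell the reader what the scale was.

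A reader might go further and infer that the AMP finding of no difference cannot be interpreted. The documents do not support that. A t-test on totals formed under one consistent rule is valid whichever maximum is printed, and inconsistency has not been shown.

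A reader might likewise infer that users and non-users were scored on different scales. The eligibility criterion "or being a non-user" shows that non-users could enrol. It does not show how many did, how they were tested, or that the condition changed between visits. Stable differences in condition between patients would also matter less if change scores were analysed, and section 4.6.b frames the outcome as change from baseline. What remains is a gap in reporting.

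Finally, adjusting for baseline does not cure a misstated maximum. That is correct. The adjustment is a separate improvement to the same comparison.

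**Conclusion.** The contradiction is real as written: 45 by the plain reading of section 4.6.b against 39 in section 4.9, a difference of 6 points, with the same 21 items on both sides and no stated rule to connect them. The figure of 45 is derived, and assumes that each of the 20 tasks can score 2. Which section is wrong cannot be settled from the documents.

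The consequence is limited to what has been left undefined: the range of a scored primary outcome, the version of the instrument, and the condition in which each patient was tested. Harm to the between-group comparison depends on patients or visits having been totalled under different rules or versions, and the documents neither show nor exclude this. This is a should-fix point.

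**What to change.** 1. Name the AMP version or versions used. Give item ranges that sum to the stated maximum, and correct whichever of sections 4.6.b and 4.9 is wrong.
2. Check every recorded total at baseline, week 2 and week 4 against that range. Where a total falls outside it or the rule is in doubt, re-total from the item scores.
3. Report for each patient whether the AMP was scored with or without a prosthesis. The trial is complete, so the condition can be reported but no longer standardised.
4. In sections 4.10 and 7, replace the unadjusted t-test for AMP with an analysis of covariance on the week-4 score, adjusted for baseline AMP. If prosthesis use was recorded, add it as a covariate in a sensitivity analysis. Results have already been reported, so say that this analysis was chosen afterwards and show the t-test result beside it.

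**Cost.** A text correction, a check of existing score sheets, and one re-analysis of data already collected. With 24 patients the t-test has 24 − 2 = 22 residual degrees of freedom. Baseline adjustment leaves 21, and adding prosthesis use leaves 20. No new patients or visits are needed.

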**6. Follow-up**

After first assessment and treatment amputees were ask to continue their exercise plan at home and reassessed after two weeks. During home-based treatments, daily telephonic reminders were given to all of the participants. Research evidence recommends that a treatment protocol of four weeks of mirror therapy may reduce chronic pain. Therefore, therapist collected the data at baseline, and before and after treatment at the end of 2nd and 4th weeks.

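### Controls were given the written phantom-exercise instructions, so they could have practised the experimental treatment; whether any did is not recorded, and the null results cannot be read as absence of effect

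*Combined protocol and SAP*

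**What the plan says.** **The contrast.** Section 4.5 (Rehabilitation protocols) gives both arms mirror therapy and routine physiotherapy; "the experimental group was given Phantom Motor Execution (PME), also known as phantom exercises, additionally (15 minutes" is the only addition.

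**The brochure.** Section 4.9 (Data collection) describes an illustrated brochure "having illustrations and detailed information about mirror therapy and phantom exercises was also provided to all participants". The next sentence says that "in both groups all the instruction given verbally or written in brochure was in native language Urdu", so the brochure is not naturally read as reaching the experimental arm only.

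**Home practice.** Section 6 (Follow-up) says "amputees were ask to continue their exercise plan at home and reassessed after two weeks", and that "daily telephonic reminders were given to all of the participants". It does not say what the calls covered or whether they differed by arm.

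**Supervision.** Section 4.5.b describes mirror therapy under a physiotherapist's "supervision every day for 4 weeks".

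**Monitoring.** Section 4.5.c advises participants to keep a log of their physical activities. No analytic use of the log is stated.

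**Results already reported.** The project summary gives significant differences favouring the experimental arm in pain and in the SF-36 bodily pain domain, and no significant between-group differences in ambulatory potential or the other SF-36 domains.

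**The concern.** If the written instructions for the only component under test are handed to the control arm, the two arms may receive more similar treatment than the design intends. The exercises in section 4.5.a need no equipment. Controls entered with phantom pain of 40 to 100 on the VAS, and people taking pain relief medication were excluded (section 4.2), so controls had a motive to try them. Section 12 credits the Urdu brochure with helping participants understand the exercises.

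What is at stake is mainly the reading of the null results. AMP is listed as a primary outcome, and seven of the eight SF-36 domains also showed no significant difference. A null could mean that phantom exercises add nothing, that 24 patients were too few, or that some controls also did the exercises. The documents give no means of separating these.

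There is a second route. A control who has read about phantom exercises can recognise that they are not part of his or her own plan. VAS and SF-36 are self-reported, so that awareness could worsen control scores and widen the differences.

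**Working it through.** **1. Could controls have practised?** Section 4.5 reserves phantom exercises for one arm, section 4.9 gives the written instructions to both, and section 6 places exercise at home. The opportunity follows from these three statements.

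**2. Is there a safeguard?** I looked for a control version of the brochure, an instruction to controls not to do phantom exercises, and a record of whether they did. None is described. The nearest items are the advised activity log (4.5.c) and the reminder calls (6), neither with a stated use for this purpose.

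**3. Can the plan's sample size anchor the effect?** Section 4.3 gives 6 per group calculated and 12 per group included, without effect size, SD, power or sidedness, so the 6 cannot be reproduced. It can only be inverted under assumptions. With two-sided alpha 0.05, 80% power and the normal approximation:

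d = √(2/6) × (1.960 + 0.842) = 0.577 × 2.802 = 1.62 SD.

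Other assumptions give 1.87 (two-sided, 90% power), 1.44 (one-sided, 80%) or 1.69 (one-sided, 90%).

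**4. What would dilution do to power?** Let c be the share of the phantom-exercise effect that the control arm also obtains. Under linear dilution the contrast is d(1 − c). With n = 12 per arm, a two-sided t-test has 22 degrees of freedom, critical value 2.074 and noncentrality d(1 − c)√(12/2). For example, d = 1.2 and c = 0.25 give 0.90 × 2.449 = 2.20, and power 0.559.

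Two effect sizes are used: 1.2 SD, an assumption chosen because 12 per arm detects it with about 80% power, and 1.62 SD from step 3.

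| c | Power, d = 1.2 | Power, d = 1.62 |
|---|---|---|
| 0 | 0.802 | 0.966 |
| 10% | 0.715 | 0.927 |
| 25% | 0.559 | 0.812 |
| 50% | 0.290 | 0.475 |

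The sample size needed to hold power grows by about 1/(1 − c)²: 1.23, 1.78 and 4.0 times at 10, 25 and 50%.

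**5. What the table does not show.** Every c is an assumption, and neither d is stated in the documents. VAS and one SF-36 domain were compared by the Mann-Whitney test, so the t-test figures are only a guide there.

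**6. Direction.** Dilution moves a difference toward zero. Awareness among controls would plausibly move self-reported differences away from zero. The documents give nothing from which to size either.

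**The case against.** **Opportunity is not occurrence.** A reader might infer that controls did practise. Nothing says so. Section 4.9 has participants guided about their own treatment plan and shown the relevant exercises, and section 6 has them continue their own plan. That wording fits arm-specific instruction, although it does not show that controls were told to abstain. This objection stands, and the point is limited to what controls could have done.

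**Controls were not necessarily unobserved.** Sections 4.5.b and 6 disagree about supervision, and a log was advised, so a flat statement that nobody could see what controls did goes too far. Nor would reconciling those sections settle the matter: supervision of a 15-minute mirror session leaves the rest of the day open either way. The contradiction is real but separate.

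**The pain finding survives dilution.** A reader might take contamination to undermine the reported pain benefit, or to bias every contrast toward no difference. Neither follows. Dilution alone would make a significant pain difference conservative, and awareness could act in the opposite direction.

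**The nulls are weak anyway.** With 12 per arm, a non-significant result is poor evidence of no effect even without contamination. True, but contamination adds a cause that a larger sample would not remove.

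**The size depends on the effect assumed.** At 25% dilution, power is 56% or 81% according to d. That is why both columns are shown and neither is offered as an estimate.

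**The trial is over.** Section 11 dates it February 2020 to March 2021. New brochures cannot help it, and controls' practice can be counted only if it was recorded. This also stands, and it shapes the remedy.

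**Conclusion.** The concern holds as a risk to the contrast that the plan created and did not monitor. As written, one brochure with detailed phantom-exercise information reached both arms, and no safeguard or specific check is described. The non-significant results for AMP and seven SF-36 domains should not be read as absence of effect. For pain the net direction of bias is unknown: dilution would understate the difference, awareness could overstate it. The documents do not support saying that contamination occurred, or that the pain result is wrong.

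The size is illustrative only. At 25% dilution, power would fall from 80% to 56% with a true effect of 1.2 SD, or from 97% to 81% with 1.62 SD; at 50%, to 29% or 48%. These figures assume linear dilution, a two-sided 5% t-test and, for 1.62 SD, that 6 per group meant 80% power. Confidence is high about what the brochure text says and low about how much dilution there was. This should be fixed, but it does not by itself invalidate the trial.

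**What to change.** **In the design, or for any repeat of it:** use two brochures, with phantom exercises only in the experimental version. Record practice in both arms through the existing log or reminder call. Word the question neutrally, for example by asking which exercises were done that day, so that it does not prompt controls to try phantom exercises. The cost is a second brochure version and one open question in a call already being made.

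**For this completed trial:**

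- State whether the brochure was identical in both arms and what controls were told about phantom exercises.
- Report any control practice found in the logs, or state that it was not recorded.
- Describe the estimate as the effect of being assigned phantom exercises in addition, when controls also held the written instructions.
- State that the null results may be diluted, and that awareness among controls could have affected VAS and SF-36.

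This costs a check of the existing logs and a few sentences of text.

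**Separately,** reconcile the daily physiotherapist-supervised mirror therapy in section 4.5.b with the home-based treatment in section 6, so that a reader can tell how much of the programme was supervised in each arm.
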